**Figure 1 F1:**
[figure not shown]
CONSORT flowchart.

### Procedures

2.5

#### Cardiorespiratory evaluation

2.2.1

Ergospirometry is currently the most accurate cardiorespiratory fitness test.^[24]^ In this study, we will use a progressive treadmill protocol, previously used by our research group,^[5,7,17]^ an ergometric treadmill model Super ATL, and a gas analyzer model VO2000 (Inbrasport, Porto Alegre - RS, Brazil), which will be connected to a microcomputer for data visualization and recording. The ergospirometry test will start with the treadmill set at 1% slope, with an initial speed of 3 km/h, which will be maintained until the end of the warm-up phase lasting 3 minutes. After the warm-up phase, the speed will be increased by 1 km/h every minute until reaching a maximum speed of 16 km/h. The end of the test will be defined by the volunteers, who will be instructed to perform the test until they reach exhaustion.^[5,7,17]^ Then, the recovery phase will begin, lasting 3 minutes at a speed of 6 km/h. In the test, data on the total time of the exercise (time to exhaustion), maximum oxygen uptake in relative values in relation to body mass (VO_2max_), and aerobic and anaerobic thresholds will be recorded.^[5,7,17]^ These data will be used to assess the performance of the subjects in the exercise protocol, as they are currently the parameters most used for this purpose in the literature.^[24]^

The entire test will be monitored by electrocardiography and blood pressure measurements. If any abnormal changes in heart rate or in blood pressure are found or if the volunteer has any complaint, the test will be discontinued and the volunteer will be excluded from the study.

#### Body composition evaluation

2.2.2

All body composition evaluations will be performed by the same technician (level II of the International Society for the Advancement of Kineanthropometry – ISAK), using the procedures established by the ISAK.^[25]^ Height, body mass, lengths of body segments, diameters, perimeters, and skinfolds will be measured to assess muscle mass, adipose mass, residual mass, bone mass, and epithelial mass.^[17]^

#### Aerobic training

2.2.3

Aerobic training will be performed on a treadmill, with and without applying PBMT, 3 times a week on nonconsecutive days, for 12 weeks. Each training session will last 30 minutes, with an intensity ranging from 85% to 90% maximum heart rate,^[17]^ which will be assessed using the cardiorespiratory evaluation protocol described above.^[7,17]^ This protocol will be interrupted when criteria established by the American Heart Association guidelines are met. The subjects will also be evaluated using the 0 to 10 Borg scale, which is a simple method for classifying perceived exertion, feeling of physical fatigue, or dyspnea.

#### Photobiomodulation therapy (PBMT)

2.2.4

PBMT or placebo will be applied before and after each training session. This irradiation protocol was tested and optimized in a previous study conducted by our research group.^[17]^ The results of this study^[17]^ showed that PBMT before and after each training session was the most effective in enhancing the effects of aerobic training. PBMT will be applied bilaterally using the direct contact method with light pressure on the skin at different sites, namely 9 sites on the knee extensor muscles (Fig. 2A), 6 sites on the knee flexor muscles, and 2 sites on the plantar flexor muscles (Fig. 2B).

**Figure 2 F2:**
[figure not shown]
(A) Irradiation sites for PBMT in anterior thigh muscles. (B) Irradiation sites for PBMT in posterior thigh muscles and plantar flexor muscles.

To apply PBMT, a 12-diode cluster will be used, including four 905 nm laser diodes (12.5 W peak power of each diode, 250 Hz), four 875 nm LED diodes (17.5 mW average power of each diode), and four 640 nm LED diodes (15 mW average power of each diode), manufactured by Multi Radiance Medical (Solon, OH). Considering the large irradiation area used in the present project, the use of diode clusters will be essential for the application of PBMT. In this study, the cluster is circular and has a total irradiation area of 20 cm^2^.

The dose used for active PBMT will be 30 J per area (228 seconds of irradiation in each area),^[10]^ 510 J irradiated energy per lower limb,^[7,12,17]^ and 1020 J total irradiated energy.^[7,12,17]^ The dose that will be used at each site was previously tested and optimized by our research group using the same PBMT device with favorable results in terms of enhancing performance and muscle recovery.^[10]^ Furthermore, the irradiation sites were also previously optimized by our research group.^[7,12,17]^ The complete description of PBMT parameters is presented in Table 1.

**Table 1 T1:**
[figure not shown]
Parameters for PBMT.

### Statistical analysis

2.6

The primary outcome will be time until exhaustion obtained from progressive treadmill test. The secondary outcomes are VO_2max_ and fat percentage test. The intention-to-treat analysis will be followed a priori. All the data will be analyzed by a blinder researcher not involved in data collection. The findings will be tested for their normality using the Shapiro–Wilk test. Parametric data will be expressed as mean and standard deviation and nonparametric data as median and respective upper and lower limits. Parametric data will be analyzed by 2-way repeated measures analysis of variance (ANOVA; time vs experimental group) with post-hoc Bonferroni correction. Nonparametric data will be analyzed using the Friedman test and, secondarily, the Wilcoxon signed-rank test. Data will be analyzed in terms of both their absolute values and their percentage of change based on the values established in the baseline. The significance level will be set at *P* < .05.

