**Methods and analyzes::**

A randomized, triple-blind, placebo-controlled clinical trial will be carried out. Healthy male volunteers will be randomly distributed into 4 experimental groups: PBMT before and after training sessions + PBMT during detraining, PBMT before and after training sessions + placebo during detraining, placebo before and after training sessions + PBMT during detraining, and placebo before and after training sessions + placebo during detraining. The aerobic endurance training sessions will be carried out using motorized treadmills during 12 weeks, and the detraining period will consist in the next 4 weeks after that. It will be analyzed the time until exhaustion, maximal oxygen uptake (VO_2max_), and fat percentage of volunteers.

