### Subjects and sample size

2.2

As no studies assessing the effects of PBMT during the detraining period after an aerobic training program are currently available, the number of participants per group in the present study was calculated based on a pilot study, with 5 volunteers per group, which was conducted by our research group in order to estimate the sample size. A β value of 20% and an α of 5% were used to calculate the sample size.

The pilot study showed that applying PBMT during the detraining period resulted in a time to exhaustion (primary outcome of this study) of 923.60 seconds (65.77 standard deviation) during the progressive treadmill test, whereas applying the placebo during the detraining period resulted in a time to exhaustion of 846.82 seconds (99.23 standard deviation). We used the Researcher's Toolkit to calculate the sample (https://www.dssresearch.com/KnowledgeCenter/toolkitcalculators/samplesizecalculators.aspx).

On the basis of the aforementioned parameters used to calculate the sample, we found 15 volunteers per group, for a total of 60 volunteers. Therefore, predicting a 20% sample loss, 72 healthy, physically inactive male volunteers aged from 18 to 35 years will be recruited for the study to ensure a final sample size of 60 volunteers. As the PBMT device used in the study causes no harmful thermal effects,^[23]^ volunteers of different skin colors will be recruited.

Volunteers will be informed about all study procedures and will be asked to sign the Informed Consent Form before their enrollment in the study.

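### A Shapiro–Wilk test on the outcome data chooses the primary analysis under a rule that can be applied in several ways, and its non-normal branch has no test between the randomised groups

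*Protocol article*

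**What the plan says.** All of the relevant text is in section 2.6 of the protocol article, apart from the design figures.

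- **Primary outcome:** "The primary outcome will be time until exhaustion obtained from progressive treadmill test".
- **Gate:** "The findings will be tested for their normality using the Shapiro–Wilk test".
- **Branch if normal:** "Parametric data will be analyzed by 2-way repeated measures analysis of variance (ANOVA; time vs experimental group) with post-hoc Bonferroni correction".
- **Branch if not normal:** "Nonparametric data will be analyzed using the Friedman test and, secondarily, the Wilcoxon signed-rank test".
- **Scales:** "Data will be analyzed in terms of both their absolute values and their percentage of change based on the values established in the baseline".
- **Level:** "The significance level will be set at *P* < .05". No separate level is given for the normality test.

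The abstract gives four groups, and section 2.4 gives five assessments (baseline and weeks 4, 8, 12 and 16). Section 2.2 sizes the trial on a difference in mean time to exhaustion. The PBMT mean is 923.60 s (SD 65.77), and "applying the placebo during the detraining period resulted in a time to exhaustion of 846.82 seconds (99.23 standard deviation").

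**The concern.** The trial's own outcome data decide which analysis of time to exhaustion is primary. The text leaves open whether the normality test is run per group and visit, per visit, once on all values or on model residuals. It also leaves open whether one rejection moves the whole outcome off ANOVA. Two analysts could follow section 2.6 faithfully and reach different primary tests. Because absolute values and percentage change are both analysed, the same outcome could take one branch on one scale and the other branch on the second.

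The two branches also answer different questions. The ANOVA contains a group effect and a group-by-time interaction. Friedman ranks each man's own visits, and Wilcoxon signed-rank compares pairs of visits within men, so neither compares the four randomised groups. A chance rejection by the gate could leave the trial with no test of its own hypothesis.

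**Working it through.** **1. The scale that sized the trial.** Section 2.2 supplies the inputs.

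- Difference: 923.60 − 846.82 = 76.78 s.
- Common SD: √[(65.77² + 99.23²)/2] = √7086.14 = 84.18 s.
- n per group = 2(z_α + z_β)² × SD²/difference², with SD²/difference² = 7086.14/5895.17 = 1.202.
- One-sided 5%, 80% power: 2 × (1.645 + 0.842)² × 1.202 = 14.9, so 15. This reproduces the plan's figure.
- Two-sided 5%: 2 × (1.960 + 0.842)² × 1.202 = 18.9, so 19.

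Sidedness is a separate matter. What counts here is that the plan's 15 per group comes from a between-group difference of means in seconds.

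**2. How often normal data fail the gate, closed form.** With k independent tests at 5% (assumed, since no level is stated) and any rejection leaving ANOVA, the probability is 1 − 0.95^k.

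| Reading of the rule | k | Leaves ANOVA |
|---|---|---|
| One test | 1 | 5.0% |
| Each group at week 16 | 4 | 18.5% |
| Each visit, groups pooled | 5 | 22.6% |
| Each group at each visit (4 × 5) | 20 | 64.2% |

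**3. The same by simulation.** The data were exactly normal, with 4 groups, 5 visits, 15 or 18 men per group, and 2,000 to 4,000 trials per setting. Within-person correlation is not given in the document, so it was varied, equal across visits.

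| Reading of the rule | Correlation | Leaves ANOVA |
|---|---|---|
| 20 cells | 0 to 0.7 | about 62% |
| 20 cells | 0.8 / 0.9 / 0.95 | 57–60% / 51–52% / 42–44% |
| 5 visits, groups pooled | 0 / 0.5 to 0.8 / 0.9 / 0.95 | 21–24% / 19–21% / 16–17% / 13–15% |
| 4 week-16 cells | 0 to 0.95 | 17–20% |
| One test on residuals with subject effects removed, on week-16 residuals, or on week 16 minus week 12 | 0.5 to 0.9 | about 4–5% |

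With correlation decaying over visits (AR(1), 0.5 to 0.9), the 20-cell reading gave 56–63%, the per-visit reading 18–22% and the week-16 reading 18–20%.

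A single test on all values pooled, with differences between men left in, is a special case. It treats repeated readings as independent, and its rejection rate rises from 5–6% at zero correlation to about 72% at 0.95.

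**4. Does the gate detect what it is meant to detect?** With 15 men, one Shapiro–Wilk test at 5% rejected in 15% of samples from a t distribution with 5 degrees of freedom. It rejected in 23% from a gamma with shape 4 and in 28% from a lognormal with sigma 0.4. It misses most such departures.

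**5. The cost of the gate on its own.** Suppose the fallback were a between-group rank test. The setting was normal data, 15 per group, AR(1) 0.8, the pilot difference and SD, a two-group comparison at week 16, two-sided 5%, and 4,000 runs.

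| Procedure | Gate fires | Type I error | Power |
|---|---|---|---|
| Always t-test | – | 4.5% | 69.0% |
| 20-cell gate | 60% | 4.6% | 66.6% |
| 4-cell gate | 18% | 4.9% | 68.5% |

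The loss is 69.0 − 66.6 = 2.4 points at most, and type I error hardly moves.

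**6. The cost with the fallback as written.** No power figure can be given for the between-group comparison on that branch, because section 2.6 names no between-group test there.

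**The case against.** **The rule is written in advance.** Both branches and the trigger are set out, and the analyst is blinded and takes no part in data collection. That stands as far as it goes: a reader might infer that the analysis is left wholly open, and it is not. What is missing is a single way of applying the rule.

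**The detail belongs in a fuller document.** The unit and level of an assumption check are often left to an analysis plan, and their absence alone would not be a finding. But the article states the decision rule and both branches. A fuller document could define the gate and still leave a branch without a between-group test; the stated rule itself has to change.

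**The high figures need assumptions.** A reader might infer that normal data would be sent off ANOVA in most trials. That requires about 20 separate tests with any rejection counting, which the text does not say. A single residual test, at about 5%, is equally compatible with it.

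**The gate alone does little harm.** This is correct: about 2 points of power and no material type I inflation for normal data, given a between-group rank fallback. The harm needs the gate and the within-subject fallback together.

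**Two further readings go too far.** One is that the Wilcoxon tests are to be uncorrected: section 2.6 is silent on this and attaches Bonferroni only to the ANOVA branch. The other is that passing the gate secures the planned power: section 2.2 sizes a two-group comparison of means, not the four-group, five-visit ANOVA with Bonferroni.

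**Conclusion.** The point holds in conditional form. Section 2.6 lets a normality test on the outcome data choose the primary analysis, without stating the unit, the number of tests or how mixed results are handled. Exactly normal data would leave the ANOVA branch in about 5% of trials with one residual test and about 64% with 20 independent cell tests and any rejection counting. Strong within-person correlation brings the 20-cell figure down to 42–44%. These figures assume a 5% level for each Shapiro–Wilk test. The spread arises from a choice that the document does not make.

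The consequence that matters is the loss of the between-group and group-by-time tests, the move from mean seconds to ranks, and the absence of a stated multiplicity correction on the second branch. This should be changed before analysis. It does not show that the trial's type I error is inflated.

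**What to change.** In section 2.6, delete the Shapiro–Wilk decision rule and put in its place text to this effect:

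> Time to exhaustion, VO2max and fat percentage will each be analysed in original units by one pre-specified mean-based group-by-time model, whatever a normality test shows. The primary result is the named between-group contrast at week 16. Model residuals will be inspected graphically. A between-group rank-based or permutation analysis of the same week-16 comparison will be reported as a sensitivity analysis and cannot replace the primary result.

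The sponsor must name the contrast. The natural candidate is PBMT against placebo during detraining, the comparison that sized the trial in section 2.2. Replacing Friedman and Wilcoxon signed-rank with a between-group rank test while keeping the gate would remove most of the harm, but the choice of effect scale would still depend on the data.

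The cost is a few sentences and no new data. The downside is some loss of efficiency if the data are grossly skewed. A rank-based sensitivity analysis would help to show this. A permutation test of the mean contrast would check the P value but would not show the efficiency lost against ranks.

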The evaluations described below will be performed before starting the protocol (baseline) and after 4, 8, and 12 weeks of aerobic endurance training, as well as after 4 weeks without training (detraining period) at 16th week. A flowchart summarizing the procedures of this study is presented in Fig. 1.

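### As written, the repeated-measures ANOVA and the post-randomization exclusions analyse completers, although the same plan promises intention-to-treat

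*Protocol article*

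**What the plan says.** Three parts of the protocol article bear on this.

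- **Principle and method (Statistical analysis).** The section states: "The intention-to-treat analysis will be followed a priori". It then says: "Parametric data will be analyzed by 2-way repeated measures analysis of variance", with time and group as the two factors and Bonferroni-corrected post-hoc comparisons. If normality fails: "Nonparametric data will be analyzed using the Friedman test and, secondarily, the Wilcoxon signed-rank test". It mentions neither imputation nor a model that accepts incomplete series.
- **Visits and expected loss.** Under Randomization and blinding and experimental groups, evaluations take place "before starting the protocol (baseline) and after 4, 8, and 12 weeks of aerobic endurance training", and "as well as after 4 weeks without training (detraining period) at 16th week". That makes five per man. Subjects and sample size recruits on this footing: "predicting a 20% sample loss, 72 healthy, physically inactive male volunteers", with the aim of ending with 60.
- **Removal after randomization.** Eligibility criteria makes inclusion depend on completing 80% or more of the procedures and excludes men injured while in the study. Cardiorespiratory evaluation excludes a man whose treadmill test is stopped for abnormal findings or a complaint. All three can be known only after allocation.

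**The concern.** Classical repeated-measures ANOVA and the Friedman test need every visit for every man, and the Wilcoxon signed-rank test needs complete pairs. A man who misses one evaluation leaves the ANOVA with all his other tests. The exclusion rules act in the same direction. Applied as written, the primary analysis therefore covers the men who finish, while the text calls it intention-to-treat.

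Two things are at stake. The first is validity: the trial's aim concerns the detraining period, so the key contrast is at week 16, where losses have accumulated. Men who leave after week 12 have a week-12 result that helps predict the missing one, and a completer analysis discards it. The second, smaller, is precision.

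**Working it through.** **Inputs.** From Subjects and sample size: 72 recruited (18 per group), 20% loss, target 60 (15 per group), α 5% with sidedness not stated, power 80%, pilot times of 923.60 s (SD 65.77) and 846.82 s (SD 99.23). Five visits. The visit correlation and the timing of dropout are not given, so they are assumed and varied below.

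**1. The plan's own figure.** The difference is 923.60 − 846.82 = 76.78 s. The sum of variances is 65.77² + 99.23² = 14,172, so the pooled SD is √(14,172/2) = 84.2 s.
- n per group = 14,172 × (z_α + z_β)² / 76.78².
- One-sided: 14.86, so 15, which reproduces the plan. Two-sided: 18.87, so 19, which does not.
- 60 × 1.2 = 72 reproduces the number recruited.

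Sidedness and the size of the inflation are separate matters and are not pursued here.

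**2. Men in a complete-case analysis.** 72 × 0.2 = 14.4 lost, leaving 57.6 (14.4 per group), about 58 men. The protocol's own target implies 72 − 60 = 12 lost.

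**3. Observed tests discarded.** Planned tests: 72 × 5 = 360.
- Loss spread evenly over the four post-baseline visits (assumed): 3.6 men each miss 4, 3, 2 or 1 tests, so 36 are missing and 324 observed. Completers supply 57.6 × 5 = 288. Discarded: 36, or 11% of those observed.
- All loss after week 12 (assumed): each lost man has 4 observed tests, so 14.4 × 4 = 57.6 are discarded.

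**4. Does the method need complete series?** A standard repeated-measures ANOVA routine, given data with one visit removed, stopped with a message that the data were unbalanced.

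**5. Bias at week 16 (illustration on assumed inputs).** No true effect, SD 84.2 s, about 20% loss after week 12, visit correlation ρ from 0.5 to 0.9.
- Dropout related to low week-12 time in one arm and random in the other: bias ≈ ρ × SD × k, where k is the upward shift, in SD units, of the mean week-12 time among men who stay. With k about 0.21, this gives 0.5 × 84.2 × 0.21 ≈ 9 s up to 0.9 × 84.2 × 0.21 ≈ 16 s. A run with slightly heavier loss in that arm (about 23%) gave 11 to 19 s.
- Same mechanism in both arms, arms alike at week 12: the completer difference stayed within about 1 s of the truth, both with no effect and with an effect of 76.78 s.

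**6. Power (two-sided, two-group comparison at one visit, Welch, pilot inputs).** SE = √(14,172/n).

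| Per group | SE (s) | Power |
|---|---|---|
| 14.4 (completers at 20% loss) | 31.4 | 65% |
| 15 (protocol's target) | 30.7 | 67% |
| 18 (nobody missing) | 28.1 | 75% |

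If all loss falls after week 12, a likelihood model that borrows from the week-12 test has variance proportional to (1 − ρ²)/14.4 + ρ²/18.
- ρ = 0.5: 0.0521 + 0.0139 = 0.0660, an effective 15.2 per group, power about 67%.
- ρ = 0.9: 0.0132 + 0.0450 = 0.0582, an effective 17.2 per group, power about 73%.

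Earlier loss leaves less to borrow, so the gain is smaller.

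**The case against.** **The conflict rests partly on silence.** The section does not say that incomplete men are dropped. Imputing missing visits before the ANOVA would reconcile it with intention-to-treat, and handling of missing data is often left to an analysis plan, which is not shown here. This stands in part. A reader might infer that the plan cannot deliver intention-to-treat at all; the document does not support that. But the article does not merely leave a detail open. It fixes a principle and a method that do not fit together as written, and its exclusion rules reinforce the misfit.

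**Completer analysis need not bias the group comparison.** A reader might infer that it is unbiased only if dropout is completely at random. That is too strong for a between-arm contrast, as step 5 shows. Blinding with an identical-looking device makes arm-dependent dropout less likely, though it does not rule it out. Nothing in the protocol shows that dropout will depend on fitness or response.

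**The power gap is not the cost of ANOVA.** Setting 65% against 75% suggests a ten-point loss from the choice of test. The 75% needs every man observed at week 16, which no analysis achieves with 20% missing. These are also single-visit, two-group powers, not powers of the time-by-group model. And the step from 60 to 57.6 comes from how the sample was inflated, not from the ANOVA. All of this stands.

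**A better model alone does not restore intention-to-treat.** This also stands. The post-randomization exclusions would defeat it under any model, and so would a rule requiring at least one post-baseline test.

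**Conclusion.** The point holds in a limited form. Followed as written, with no imputation, the primary analysis is of completers: about 58 of 72 men at 20% loss, 60 on the protocol's own planning. The rules on procedures completed, injury and stopped tests remove men after randomization as well. This conflicts with the stated intention-to-treat principle and should be corrected, but it does not show that the trial's result will be biased.

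The size depends on assumptions. The 9 to 16 s distortion, roughly 12% to 21% of the planned 76.78 s (9/76.78 and 16/76.78), needs fitness-related dropout in one arm and not in the other; with a common mechanism it is close to nil. The recoverable power is about 2 to 8 percentage points (65% to 67–73%) when all loss falls after week 12 and ρ lies between 0.5 and 0.9, and less otherwise. The main reasons to change are coherence with the stated principle and use of data already collected.

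**What to change.** 1. For time to exhaustion, replace the ANOVA with a likelihood-based mixed model for repeated measures: REML, unstructured covariance across visits, Kenward-Roger degrees of freedom, with terms for group, visit, group by visit and baseline time to exhaustion. Take the week-16 contrast from this model. The Friedman/Wilcoxon branch should not take over for this outcome, since it brings the complete-data requirement back.
2. Analyse all randomized men in the group to which they were allocated, with whatever data they have. One way is to keep baseline in the outcome vector with a mean common to all groups, which adjusts for baseline and retains men who have only a baseline test.
3. State that the criteria in Eligibility criteria (procedures completed, injury during the study) and in Cardiorespiratory evaluation (test stopped) do not remove a man from the analysis set. Whether he stops study procedures is a separate clinical matter, on which no change is suggested.

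**Cost.** Analysis wording and standard software, with no change to visits or recruitment. The model relies on data being missing at random given the observed tests, which the data cannot confirm. The gain in power is modest.

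### Optional refinement: section 2.6 fixes single-step Bonferroni for the post-hoc comparisons, where Holm's step-down procedure would give a modest gain in pairwise power at the same familywise 5%

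*Protocol article*

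**What the plan says.** Section 2.6 (Statistical analysis) names time to exhaustion as the primary outcome and, for data judged normal, a "2-way repeated measures analysis of variance (ANOVA; time vs experimental group) with post-hoc Bonferroni correction". It adds: "The significance level will be set at *P* < .05". It does not list the comparisons that form the family, does not say whether tests are one- or two-sided, and plans means and SDs rather than simultaneous confidence intervals.

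Section 2.2 (Subjects and sample size) supplies the only effect estimate. In the pilot, PBMT during detraining gave "923.60 seconds (65.77 standard deviation) during the progressive treadmill test", while "applying the placebo during the detraining period resulted in a time to exhaustion of 846.82 seconds (99.23 standard deviation"). On planning error rates it says: "A β value of 20% and an α of 5% were used to calculate the sample size". The result is: "we found 15 volunteers per group, for a total of 60 volunteers". Section 2.4 defines the four arms: A (PBMT in training and in detraining), B (PBMT, then placebo), C (placebo, then PBMT) and D (placebo throughout).

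**The concern.** Four arms give six pairwise comparisons at any one visit. Single-step Bonferroni holds each of them to alpha/6, however many of the others are already clearly significant. Holm orders the P values and tests them against alpha/6, alpha/5, and so on up to alpha/1, stopping at the first failure. It controls the familywise error under any dependence between the tests and can never reject less than Bonferroni.

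The design is one where a step-down method can help. The omnibus time-by-group test does not say which arms differ, so the question of PBMT against placebo during detraining falls to pairs such as A-B and C-D. If PBMT works in detraining, A-B, A-D, C-B and C-D all differ together. Once one pair is rejected, Holm relaxes the threshold for the rest. What is at stake is some power for individual pairwise conclusions; the validity of the analysis is not in question.

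**Working it through.** **Inputs from the documents.** Pilot means 923.60 and 846.82 s, SDs 65.77 and 99.23 s, 15 per group, four groups, alpha 5%, power 80% (section 2.2); Bonferroni at the 5% level (section 2.6).

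**Assumptions.** The family is the six between-group pairs at week 16. Tests are two-sided t tests with a pooled error on 4 × (15 − 1) = 56 df.

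**The plan's own figure.** Difference = 923.60 − 846.82 = 76.78 s. Root-mean-square SD = √[(65.77² + 99.23²)/2] = 84.18 s. n per group = 2 × [84.18 × (z for alpha + z for power)/76.78]².
- One-sided 5%: 14.86, rounded up to 15. This reproduces the stated size.
- Two-sided 5%: 18.87, rounded up to 19.

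So 15 per group matches one unadjusted, one-sided comparison. That is a separate matter from the correction method, but it sets the power from which any correction starts.

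**Smallest significant difference at each step.** Standard error of a PBMT-placebo pair = √[(65.77² + 99.23²)/15] = 30.74 s. Multiply by the two-sided t quantile on 56 df.

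| Divisor of alpha | t | Difference needed |
|---|---|---|
| 6 (every Bonferroni test; Holm's first step) | 2.735 | 84.1 s |
| 5 | 2.667 | 82.0 s |
| 4 | 2.581 | 79.3 s |
| 3 | 2.468 | 75.9 s |
| 2 | 2.303 | 70.8 s |
| 1 (Holm's last step) | 2.003 | 61.6 s |

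An observed difference equal to the pilot's gives t = 76.78/30.74 = 2.50, P about 0.015. The first step needs P ≤ 0.05/6 = 0.0083. If 76.78 s is the largest contrast, Holm therefore stops at once and rejects nothing, as Bonferroni does. Such a difference passes under Holm only from the fourth step on (divisor 3), after three other pairs have been rejected.

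**Power by simulation (40,000 trials per scenario).** With a common SD of 84.18 s, averaging over the pairs whose true difference is 76.78 s:

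| True pattern | Bonferroni | Holm | Gain (points) | At least one significant pair, both methods |
|---|---|---|---|---|
| Only A differs | 41.3% | 43.9% | about 3 | 65.9% |
| A and C above B and D | 41.1% | 45.2% | about 4 | 74.2% |
| Additive training and detraining effects of 76.78 s each | 41.4% | 49.4% | about 8 | 98.8% |

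Under the complete null, the familywise error is 4.0% for both methods.

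With the pilot SDs (65.77 s in A and C, 99.23 s in B and D) and A and C above B and D, as Bonferroni / Holm / Shaffer:
- A-B significant: 42% / 46% / 49%.
- A-B and C-D both significant: 18% / 25% / 28%.
- All four PBMT-placebo pairs significant: 12% / 19% / 20%.

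Shaffer's version uses the logical constraints among all six pairs (divisors 6, 3, 3, 3, 2, 1).

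**Distance from 80%.** By normal approximation, a two-sided test at 0.05/6 with 15 per group has 44% power (about 41% with t tests), and 80% would need 30 per group. Holm's 44% to 49% leaves most of that gap open.

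**The case against.** The strongest reply is that nothing here is wrong. Bonferroni protects the 5% familywise level, it is fixed in advance, and no other part of the protocol contradicts it. That a more powerful valid procedure exists can be said of almost any plan that names Bonferroni. This stands, and it is why the point is an improvement and not a correction.

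A reader might go further and infer that the plan gives away power on the primary outcome for nothing. The documents do not support that, for three reasons:
- The time-by-group ANOVA test does not depend on the post-hoc method, and the chance of at least one significant pair is identical because both methods begin at alpha/6.
- The 84 s threshold, against a pilot difference of 76.8 s, can look like the price of Bonferroni. Holm's first step has the same threshold.
- Bonferroni has simple simultaneous intervals that match its tests, and Holm does not. That is a real reason to prefer Bonferroni when estimation matters, though section 2.6 plans no such intervals.

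The size of the gain is also open to challenge. Section 2.6 does not define the family. There are five assessment times, and post-hoc tests may also be within group. The calculation uses single-visit t tests, not the repeated-measures model. The larger gains belong to joint results (both pairs, or all four) that the protocol does not set as success criteria, or to an assumed additive training effect that it does not quantify. These objections limit the figures. They do not touch the dominance itself, which holds for any family.

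**Conclusion.** The point holds as a cheap, optional improvement. For test decisions Holm dominates the stated correction at the same familywise 5%, whatever the family. Under the assumed six-pair week-16 family, with 15 men per arm, pilot-based effects and two-sided tests, the gain for a single true pair is about 3 to 8 percentage points, and the chance of confirming the effect in both A-B and C-D rises from about 18% to 25%. These figures are illustrative, and the gain in the repeated-measures analysis actually planned cannot be computed from the documents.

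It would be wrong to read this as an invalid analysis, or as a remedy for the trial's power. Pairwise power stays near 44% to 49%, against a planned 80%.

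**What to change.** In section 2.6, for the parametric analysis, replace the Bonferroni phrase with: *post-hoc comparisons with Holm step-down adjusted P values, familywise error 5%*. Make the change before unblinding. Shaffer's version is an alternative only if the family is exactly all six between-group pairs; it gains slightly more.

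The cost is one phrase, and standard software computes the adjusted P values. No participants, visits or procedures are added. The downside is that Holm has no simple matching simultaneous confidence intervals, so any intervals would be reported unadjusted or at the Bonferroni level, and labelled as such. If the sponsor wants simultaneous intervals that agree with the tests, keeping Bonferroni is defensible.
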